## Discussion

Symbotex™ Composite Mesh is specifically designed to incorporate a monofilament polyester mesh with an absorbable collagen film. The collagen film acts to prevent bowel adhesions and subsequent complications, such as fistula formation, and thus provides a mesh safe for intraperitoneal use [10].

A current focus in the discussion on laparoscopic management of incisional hernia repair is the pain that patients experience after surgery. It is though that the tacks used to fixate the mesh are a contributing factor and many methods have been trialed to reduce the pain. TACKoMESH will attempt to determine whether the use of a more perpendicular fixation technique to the abdominal wall will help reduce the pain experienced by patients and hence enhance their recovery, which will inevitably reduce the amount of analgesia used in the post-operative period as well as the net benefit to the health of the economy.

All previous studies [11–13] have described the use of a non-articulating mesh fixation device. The Study uses a device with an articulating arm (ReliaTack™) and will therefore provide information on any possible variances in effect at operation; mesh fixation time and other intraoperative ergonomics. More importantly it will demonstrate whether a more perpendicular trajectory of tack to peritoneum will translate into less post-operative pain.

As no study to date has examined the effects of an articulating arm it is impossible to predict the outcome of the Study. Power calculations have taken many factors and permutations into consideration and a decision made that, to detect a difference of 1 between the two groups with a dropout rate of 5%, 136 patients will need to be randomized.

Secondary outcome measures were decided as per previous trials with the knowledge that seroma formation and classification [11–13] will be a necessary morbidity that requires documentation. This will be done as per a recently established classification system designed specifically for patients undergoing laparoscopic ventral hernia repair [14].

To the authors knowledge this is the first randomized trial for laparoscopic incisional hernia that will involve fascial closure and although fixation with absorbable and non-absorbable tacks have already been compared, this will have the novel addition of one of the fixation devices having an articulating arm.

Thus, the use of ReliaTack™, as a one-of-a-kind mesh fixation device with articulating arm that can deploy spiral absorbable tacks in the TACKoMESH study aims to provide level one evidence on the safety, efficacy and ease of use of this product as well as its effects on post-operative pain and other clinical observations and outcomes.

In conclusion, TACKoMESH is a randomised controlled trial that will provide important information on the effects of repairing an incisional hernia after fascial closure with an IPOM mesh (Symbotex™ Composite Mesh). It will compare the use of an articulating, mesh-fixation device that deploys absorbable tacks with a straight-arm, mesh-fixation device that deploys non-absorbable tacks measured by pain at 30 days and an overall assessment of the safety and efficacy.

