## Abstract

**Background:**

Minimally invasive incisional hernia repair has been established as a safe and efficient surgical option in most centres worldwide. Laparoscopic technique includes the placement of an intraperitoneal onlay mesh with fixation achieved using spiral tacks or sutures. An additional step is the closure of the fascial defect depending upon its size. Key outcomes in the evaluation of ventral abdominal hernia surgery include postoperative pain, the presence of infection, seroma formation and hernia recurrence. TACKoMESH is a randomised controlled trial that will provide important information on the laparoscopic repair of an incisional hernia; 1) with fascial closure, 2) with an IPOM mesh and 3) comparing the use of an articulating mesh-fixation device that deploys absorbable tacks with a straight-arm mesh-fixation device that deploys non-absorbable tacks.

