**Methods:**

A prospective, single-centre, double-blinded randomised trial, TACKoMESH, will establish whether the use of absorbable compared to non-absorbable tacks in adult patients undergoing elective incisional hernia repair produces a lower rate of pain both immediately and long-term. Eligible and consenting patients will be randomized to surgery with one of two tack-fixation devices and followed up for a minimum one year. Secondary outcomes to be explored include wound infection, seroma formation, hernia recurrence, length of postoperative hospital stay, reoperation rate, operation time, health related quality of life and time to return to normal daily activity.

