### Rationale

To date no randomised controlled trial has compared the use of absorbable or non-absorbable tack fixation for laparoscopic incisional hernia repair after fascial closure. This prospective randomised controlled trial proposes to assess pain scores as a primary measure to determine whether absorbable tacks may provide a benefit in reducing the risk of immediate and long-term pain. Additional evaluation will see whether the risk of serious adverse events (SAE) is affected. This information is needed to provide evidence of the optimal method for surgeons and policy makers.

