### Objectives

#### Primary objectives

To compare pain measured at rest and at activity with a visual analogue scale (VAS) at day 30 post-operation incurred from using absorbable tack fixation versus non-absorbable tack fixation with a composite mesh for the repair of midline abdominal incisional hernia in adult patients.

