### Trial randomisation

There will be two arms to the trial (*n* = 136):Mesh placement with absorbable tack fixation.Mesh placement with non-absorbable tack fixation.

Participants will be allocated in sequence to a unique identification number and randomised to one of two groups i.e. receive either absorbable or non-absorbable tack fixation, stratified by defect size (3-6 cm or > 6-10 cm). The participant randomisation procedure is shown below.

Patients who have given consent and are due to be operated on will be randomised by a sealed envelope randomisation.

The operating surgeon will select from the sealed envelopes the tack to be used for the TACKoMESH Trial on the morning of the patient’s planned surgery to obtain the randomisation allocation to treatment. The patient’s initials and date of birth will be entered into the randomisation allocation; a study number and the treatment allocation assigned to each patient. The study number and treatment allocation will automatically appear on the Study Randomisation Form. Following the appropriate procedure the completed online Study Randomisation Form will be printed by the operating surgeon, placed in a provided sealed envelope, and labelled as ‘TACKoMESH - Study Randomisation Form and Incisional Hernia Repair Operation Note’.

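### The two arms differ in both tack material and device, so the trial compares two fixation systems and cannot credit a pain difference to absorbability or to tack trajectory alone

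*Protocol article*

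**What the plan says.** The protocol article describes the randomised comparison in three ways.

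- **As a package.** The Abstract's Background speaks of "comparing the use of an articulating mesh-fixation device that deploys absorbable tacks with a straight-arm mesh-fixation device that deploys non-absorbable tacks". The final paragraph of the Discussion says: "It will compare the use of an articulating, mesh-fixation device that deploys absorbable tacks with a straight-arm, mesh-fixation device that deploys non-absorbable tacks". The Discussion also states that "this will have the novel addition of one of the fixation devices having an articulating arm", so articulation is present in one arm only.
- **As tack material.** The Abstract's Methods say the trial "will establish whether the use of absorbable compared to non-absorbable tacks in adult patients undergoing elective incisional hernia repair" lowers pain. The Rationale gives the purpose as "to determine whether absorbable tacks may provide a benefit in reducing the risk of immediate and long-term pain". The Primary objectives compare day-30 pain "incurred from using absorbable tack fixation versus non-absorbable tack fixation with a composite mesh". The Trial randomisation section labels the arms by tack alone: patients "receive either absorbable or non-absorbable tack fixation, stratified by defect size (3-6 cm or > 6-10 cm" groups.
- **As trajectory.** The Discussion says: "More importantly it will demonstrate whether a more perpendicular trajectory of tack to peritoneum will translate into less post-operative pain". An earlier paragraph of the Discussion, more cautiously, says the trial will try to find out whether more perpendicular fixation eases pain.

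The Statistical analysis section plans an ANOVA of day-30 VAS with two factors, study group and defect size. There is no device or trajectory factor, and the article does not list the joint change of tack and device as a limitation.

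**The concern.** Two features change together between the arms, and the article draws a separate causal statement about each from the same single contrast. Either feature could in principle produce the whole difference. If the objective stands as worded, a positive result would be reported as evidence for absorbable tacks, and under the Discussion also as evidence for a perpendicular trajectory. A reader could then carry the result over to absorbable tacks on a straight-arm device, or to articulation with other tacks, and the trial tests neither combination. The Rationale addresses surgeons and policy makers and the Discussion promises top-level evidence on a named product, so what the result is said to show matters.

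**Working it through.** **Inputs.** Arm definitions: Abstract (Background) and Discussion. Model: Statistical analysis. Two-sided alpha 0.05: Sample size and Statistical analysis. Power 80%, SD 2, difference 1, dropout 5%, N = 136: Sample size.

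**1. The plan's own figure.**
- Normal approximation: n per arm = 2 × (1.960 + 0.842)² × 2² / 1² = 62.8, so 63. Allowing for dropout, 63 / 0.95 = 66.3, so 67 per arm and 134 in total.
- t-test: 63.8, so 64 per arm. Then 64 / 0.95 = 67.4, so 68 per arm and 136 in total, an exact match.

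The sample size is not at fault.

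**2. What the contrast estimates.** Let T = 1 for absorbable tacks and D = 1 for the articulating device, with effects t and d on pain reduction. Write the expected reduction as m + t·T + d·D.
- Articulating/absorbable arm: T = 1, D = 1, giving m + t + d.
- Straight-arm/non-absorbable arm: T = 0, D = 0, giving m.
- Difference between arms: t + d.

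If the two features also interact, that term joins the same sum.

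**3. Identifiability.** The design matrix has three columns (intercept, T, D), but T and D are equal for every patient. A check with 68 rows per arm gives rank 2 for 3 parameters. Defect size, the other ANOVA factor, adds a column of its own and does nothing to distinguish T from D. More patients add rows of the same two kinds, so the rank does not rise.

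For comparison, crossing tack with device in a 2×2 layout gives rank 3, so both main effects could be estimated if they do not interact. This is only an illustration, since the article does not say whether either device can deploy the other type of tack.

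**4. What the data could distinguish.** Power by the normal approximation, with 64 evaluable patients per arm:

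| Tack effect t | Trajectory effect d | Expected difference | Power |
|---|---|---|---|
| 1 | 0 | 1 | 81% |
| 0 | 1 | 1 | 81% |
| 0.5 | 0.5 | 1 | 81% |
| 1.5 | −0.5 | 1 | 81% |

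The four rows have the same expected difference and the same power. A trial that observes 1 point cannot choose between them.

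**The case against.** The strongest reply is that the package is disclosed and that comparing packages is legitimate. The Abstract's Background and the closing conclusion name both features of each arm. The Abstract's Methods say patients are randomised between two fixation devices, and the Surgical technique section says the mesh is fixed with the device allocated at randomisation. On this reading the tack labels in the Primary objectives and Trial randomisation are shorthand for the two arms. The language is also not uniformly firm: the Rationale speaks only of a possible benefit, and one of the two Discussion statements only of an attempt.

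Much of this stands. The bundle is not hidden, the conclusion is correctly worded, and the randomised contrast is sound. What does not stand is that shorthand cures the problem. The Abstract's Methods promise to establish an absorbability effect and the Discussion promises to demonstrate a trajectory effect, and both promises rest on one contrast. Nor can the device difference be set aside as incidental. The Discussion says the result cannot be predicted because articulation has not been studied, so the article itself treats articulation as able to affect the outcome.

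A reader might infer more than the document supports:

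- *That the primary question cannot be answered.* It can, for the two systems as used. Only the attribution to one component fails.
- *That a null result would conceal opposing effects.* This is algebraically possible, but nothing in the article suggests that the two features act in opposite directions on pain.
- *That the article claims a randomised test of fascial closure or of the mesh.* The Abstract's Discussion refers broadly to evaluating several technical considerations, but fixation devices are among those it lists. The Rationale and the conclusion present fascial closure as the common setting.

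**Conclusion.** The point holds as one of attribution. The trial validly tests an articulating device with absorbable tacks against a straight-arm device with non-absorbable tacks. It cannot separate the effect of absorbability from that of a more perpendicular trajectory, at 136 patients or at any other number. Within the observed sum the share due to either feature is undetermined. This rests only on the arm definitions printed in the article and on there being no arm that crosses tack with device; it needs no assumption about the size or direction of either effect. A full protocol or analysis plan could not rescue the two claims, because no analysis of these two arms recovers the separate effects. The fault is confined to wording, but that wording includes the primary objective and so governs what a positive result may be said to show.

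**What to change.** 1. Restate the aim in the Abstract's Methods, the purpose in the Rationale, the Primary objectives and the arm labels in Trial randomisation as a comparison of the two fixation systems, naming device and tack together for each arm. The Abstract's Background and the closing conclusion already provide the wording to match.
2. In the Discussion, delete or reword both statements that the trial will determine or demonstrate the effect of perpendicular trajectory on pain. Trajectory may remain as a possible explanation that the design does not test.
3. Add one sentence to the limitations: tack material and device change together, so their separate effects cannot be estimated.

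The closing conclusion, the sample size of 136 and the planned analysis stay as they are. The cost is editorial, plus a narrower headline claim.

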## Abbreviations

ANOVA: Analysis of variance
BMI: Body mass index
CRF: Case report form
DC: Double crown
IPOM: Intraperitoneal On-lay mesh
IQR: Interquartile range
NHS: National Health Service
PIS: Patient information sheet
QoL: Quality of life
RCT: Randomised controlled trial
SAE: Serious adverse effects
SC: Single crown
SD: Standard deviation
SSI: Surgical site infection
UK: United Kingdom
VAS: Visual analogue score
